## Abstract

**Background:** Age is a key determinant for the development of cardiovascular disease and higher age coincides with an increased prevalence of obesity and physical inactivity. The study examines the influence of physical activity on aging processes of physiological systems focusing on the mechanisms of vascular aging.

**Methods/Design:** The study consists of two parts. The cross-sectional approach aims at examining the association of physical fitness and cardiovascular risk with large and small artery function in healthy older active (HOA, *n* = 40) and sedentary (HOS, *n* = 40) persons as well as older sedentary individuals with increased cardiovascular risk (OSR, *n* = 80) aged 50–80 years. In the interventional approach, the OSR group is randomized into a 12-week walking-based high intensity interval training (HIIT) group or a control condition, aiming at examining the effects of HIIT on arterial function in diseased older adults. Active lifestyle is defined as >9 metabolic equivalent of task (MET) per week and sedentary as ≤3 MET/week. Inclusion criteria for OSR are overweight or obesity (body mass index ≥30 kg/m^2^) plus at least one additional cardiovascular risk factor. The primary outcome is arterial stiffness as determined by aortic pulse wave velocity (PWV). The secondary outcomes are retinal arterial and venous diameters. Further cardiovascular assessments include peripheral PWV, central haemodynamics, retinal endothelial function, carotid intima media thickness, cardiac strain and diastolic function as well as autonomic function and inflammation. Physical fitness is measured by a treadmill-based spiroergometry to determine peak oxygen uptake.

**Discussion:** The aim of the study is to demonstrate the importance of and need for specific physical activity programs for seniors to achieve healthier aging as a long-term goal. Vascular function defines disease- and age-related end organ damage and represents the potential to contain health at older age. This research will identify cardiovascular biomarkers that best resemble underlying cardiovascular risk in age and disease. The integrated approach will help define new recommendations for treatment guidance of exercise therapy in an aging population.

ClinicalTrials. gov: NCT02796976; registered 02 June 2016 (retrospectively registered).

## Background

Atherosclerotic cardiovascular disease (CVD) is a chronic inflammatory disease of the circulatory system and it is a main health care threat in western countries. Almost every third death can be attributed to CVD, amounting to a total of 17.5 million associated deaths worldwide (World Health Organization, 2014). About 80% of CVD deaths are thought to be associated with arterial disorders (Thom et al., 2006). Age is one of the major risk factors for the development of CVD and demographic change further aggravates the enormous socio-economic health care challenge. The number of persons aged 60 or older will double until the year 2050, which will further aggravate the burden of age-related diseases such as CVD (World Population Prospects, 2015). Aging is associated with complex structural and functional alterations of the vascular bed (Ferrari et al., 2003).

The rise of the obesity epidemic in the last decades is another main underlying reason for the high prevalence of CVD. To date, almost 70% of adults are classified as either overweight or obese as compared to 40% 40 years ago (Lavie et al., 2009). The prevalence of obesity and the metabolic syndrome increases with older age (Ford et al., 2004). Physical inactivity is a main risk factor not only for the development of obesity but also for non-communicable diseases in general and CVD specifically. The World Health Organization (WHO) has stated that more than three-quarters of all CVD mortality may be prevented by appropriate changes in lifestyle. Blair et al. found that individuals who improved from unfit to fit over a mean follow-up of 5 years showed a reduction in mortality risk of 44% compared to those who remained unfit (Blair et al., 1995). In a large prospective cohort, Wen et al. reported a 14% reduction of all-cause mortality in individuals exercising for 90 min per week or 15 min per day compared to an inactive group (Wen et al., 2011). Vigorous-intensity exercise (>8.5 MET) seemed to yield greater health benefits in terms of all-cause mortality reduction than moderate-intensity exercise (4–6 MET).

High intensity interval training (HIIT) has been suggested to be an effective training modality for secondary prevention of CVD in older adults and seems to be superior to well-established moderate continuous exercise training with respect to improving not only cardio respiratory fitness but also the cardiovascular risk profile (Helgerud et al., 2007; Wisloff et al., 2007; Tjonna et al., 2008; Guimarães et al., 2010; Kessler et al., 2012; Molmen et al., 2012). The risk of CVD events is considered to be equally low for both HIIT and moderate continuous training (MCT) intervention strategies (Rognmo et al., 2012). Exercise training and regular PA are able to reduce the main underlying mechanisms for the development and progression of CVD such as inflammation, oxidative stress and endothelial dysfunction. However, it is still unclear which biomarker is most suitable to detect the process of vascular aging and can sensitively quantify and monitor treatment effects at older age. Novel approaches for cardiovascular risk screening and exercise treatment strategies are indispensable to counteract the growing socio-economic burden and health hazard of cardiovascular disease in an aging population.

## Cardiovascular health and aging: a systems physiology approach

Vascular aging is a gradual process of the circulation that is aggravated by the development of cardiovascular risk factors and affects both the macro- and microcirculation (Nichols et al., 2011). Since aging is the main denominator for chronic CVD manifestations, the concept of vascular aging has been proposed to improve clinical guidance of patients with increased cardiovascular risk (Nilsson et al., 2009, 2013). The concept implies that age-related clinical or subclinical manifestations are associated with vascular alterations, which can be quantified by sensitive non-invasive vascular assessments. Consistent evidence suggests that arterial stiffness is a subclinical, strong and valid vascular biomarker for the quantification of atherosclerosis and grave cardiovascular dysfunction (Salomaa et al., 1995; Laurent et al., 2006; Vlachopoulos et al., 2010a). Arterial stiffness and the impairment of the buffer capacity of large arteries lead to elevated left ventricular afterload and left ventricular hypertrophy and, at later stages, to heart failure, worsening of coronary artery disease and increased risk of stroke (Hamilton et al., 2007). Aortic pulse wave velocity (PWV), acknowledged as the “gold-standard” method for measuring arterial stiffness, is an independent predictor for cardiovascular morbidity and mortality in the general population, elderly subjects and in patients with cardiovascular disease (Laurent et al., 2001; Sutton-Tyrrell et al., 2005; Hansen et al., 2006; Mattace-Raso et al., 2006). An increase of aortic PWV by 1 m/s has been reported to represent a risk increase of 15% in total cardiovascular and all-cause mortality (Vlachopoulos et al., 2010a). In the Baltimore Longitudinal Study of Aging, aortic PWV increased twofold across the age span and higher fitness were associated with reduced arterial stiffness in a predominantly sedentary population as well as in endurance trained older men compared to less active peers (Vaitkevicius et al., 1993). In a population-based study of 373 younger subjects in the Netherlands, it was found that the effect of habitual PA on arterial stiffness depends on its intensity and differs depending on the arterial tree segment. Vigorous but not light-to-moderate habitual PA provides favorable associations with peripheral arterial stiffness in young adults (van de Laar et al., 2011). In our study, different approaches of measuring arterial stiffness are applied in various vascular beds. Central and peripheral PWV measurements are performed as well as 24-h monitoring of central haemodynamics such as augmentation index (AIx) and pulse pressure (PP). Assessment of the macrocirculation includes the structural analysis of the carotid intima-media thickness (IMT).

It is generally assumed that increased central PWV contributes to the pathogenesis of small vessel disease, particularly the myocardial and cerebral microcirculation. Increased arterial stiffness seems to expose small vessels to highly pulsatile pressure and flow, thereby inducing damage to the microvascular bed (O'Rourke and Safar, 2005). A cross-talk between large and small arteries exists, promoting a vicious circle of increases in peripheral vascular resistance, blood pressure and arterial stiffness, eventually leading to the manifestation of micro- and macrovascular target organ damage (Laurent et al., 2009). Retinal vessel analysis is a non-invasive technique that allows the examination of the retinal microcirculation (Liew et al., 2008). Retinal vessels are part of the cerebrovascular bed and they are affected early in the process of cardiovascular disease. Large cohort studies have previously shown that narrower retinal arterioles, wider retinal venules and a resulting lower arteriolar-to-venular diameter ratio (AVR) are associated with increased risk and severity of hypertension (Wang et al., 2003; Wong et al., 2004a; Ikram et al., 2006b), risk of stroke (Ikram et al., 2006a; McGeechan et al., 2009) and a higher cardiovascular morbidity and mortality in older subjects (Wong et al., 2002; Wang et al., 2007). In older adults, obesity is associated with retinal venular widening and a lower arteriolar-to-venular diameter ratio (AVR) (Nguyen and Wong, 2006; Wang et al., 2006). Inflammation has been associated with wider retinal venular diameters (Klein et al., 2006). We have previously shown that higher physical fitness levels are associated with higher retinal AVR and that regular endurance exercise induced arteriolar dilatation as well as venular constriction, leading to a significantly improved AVR in middle-aged lean and obese individuals (Hanssen et al., 2011). Retinal microvascular endothelial function can directly be measured *in vivo* by dynamic retinal vessel imaging inducing neurovascular coupling by flicker stimulus (Falsini et al., 2002; Polak et al., 2002). An impaired response to flicker light has been associated with type 2 diabetes mellitus (Mandecka et al., 2007; Sörensen et al., 2016), high blood pressure (Nagel et al., 2004) and aging (Pemp et al., 2009; Kotliar et al., 2011). The assessment of retinal vessel diameters is used to define microvascular aging at older age and to examine associations with physical fitness. Retinal vessel analysis allows for the investigation of the cross-talk between large and small arteries.

Large artery stiffness is not only associated with small vessel disease but is known to relate to left ventricular hypertrophy as well as systolic and diastolic dysfunction (Roman et al., 2000; Weber et al., 2008; Namba et al., 2016). In patients with normal ejection fraction, increased pulse wave reflection and PWV are associated with higher left ventricular filling pressures (Weber et al., 2008). In patients with asymptomatic diastolic dysfunction, increased PWV has been shown to precede the onset of manifest heart failure with preserved ejection fraction (Karagodin et al., 2017). Indices of systolic and diastolic function share its predictive character with arterial stiffening (Vlachopoulos et al., 2010b; Kane et al., 2011; Lam et al., 2011). This suggests that ventricular-vascular interactions play a pivotal role in the clinical relevance of arterial stiffness (Chung et al., 2010). The recent Health ABC Study, however, demonstrated that the association of arterial stiffness with the development of heart failure is not independent of cardiovascular risk factors (Pandey et al., 2017). Additional assessment of left ventricular structure and function allows for analysis of the cardiovascular cross-talk and its association with cardiovascular risk factors.

Autonomic function (AF) is a principal regulator of vascular properties and cardiac function. AF alters with age and plays a crucial role in the development of cardiovascular diseases (1996; Fisher et al., 2009). Its sympathetic and parasympathetic branches regulate vascular tone and, thereby, modulate arterial stiffness (Perkins et al., 2006). Heart Rate Variability (HRV) is an easily recordable clinical marker for autonomic function and its indices have shown predictive value for the development of cardiovascular disease (1996; Kleiger et al., 2005). Increased physical activity has been shown to be associated with favorable autonomic function in older adults (Soares-Miranda et al., 2014). In addition to the above mentioned physiological systems, we will measure circulating anti- as well as pro-inflammatory cytokines and analyse their role in mediating physical inactivity- and obesity-related vascular and systemic impairments. Vascular aging and immunosenescence are explained in large part by an imbalance between inflammatory and anti-inflammatory processes. These result in a predominantly pro-inflammatory status that has been termed “inflamm aging” (Franceschi et al., 2007). Healthy aging and longevity are the result of an efficient lifelong anti-inflammatory activity that, once it fails to overcome cellular and systemic inflammatory processes, can be the driving force for frailty and age-related pathologies.

## Methods/design

### Objectives

The aims of the study are twofold. In our cross-sectional research approach, the association of physical activity and fitness on the process of normal (healthy) aging is analyzed by comparing the group of healthy older sedentary (HOS) with healthy older active (HOA) adults. The association of CVD on the process of aging is examined by comparing HOS with older sedentary persons with increased cardiovascular risk (OSR). In the interventional approach, the reversibility of advanced vascular and systemic aging by a walking-based HIIT is examined in OSR.

### Cross-sectional (part I)

Aim 1: To determine the associations of physical fitness and cardiovascular disease with large and small artery function in HOA, HOS as well as OSR group.

### Interventional (part II)

Aim 2: To examine the effects of HIIT on large and small artery function in OSR.

### Outcome measures

Primary outcome: central (carotid-femoral) pulse wave velocity (cfPWV)

Secondary outcomes: central retinal arteriolar (CRAE) and venular (CRVE) diameters

Further outcomes: peripheral (femoral-posterior tibial) pulse wave velocity (ftPWV); central augmentation index (cAIx); central pulse pressure (cPP); 24 h AIx (24AIx) and cPP (24cPP); carotid intima media thickness (IMT); retinal vessel flicker response (DVA); left ventricular diastolic function and myocardial strain; heart rate variability (HRV), inflammation.

### Hypotheses

Hypothesis 1 (Part I): cfPWV is lower in HOA compared to HOS

Hypothesis 2 (Part I): cfPWV is higher in OSR compared to HOS

Hypothesis 3 (Part II): cfPWV in OSR can be reduced by 12 weeks of HIIT compared to controls.

The same hypotheses will be addressed for the secondary and further outcomes.

### Study design

The study design consists of two parts with separate sample size considerations for the cross-sectional and interventional approach. HOA and HOS participants as well as OSR are recruited and enrolled in the cross-sectional study (Figure 1). Recruitment of the OSR group is performed on the basis of agreement to take part in the exercise intervention following the cross-sectional assessment, which serves as a baseline examination for the consecutive intervention. Before enrolment, subjects are medically examined and scanned for inclusion and exclusion criteria by the study physician. Written informed consent is obtained from eligible subjects and a medical examination and anthropometry are performed and physical activity levels are assessed. In addition, blood sampling and 24 h blood pressure monitoring including central PWV, Aix, and PP are undertaken (visit 1). The enrolment decision is taken on the basis of the inclusion and exclusion criteria. On two separate visits and in randomized order, the main vascular diagnostics, echocardiography, autonomic function and the assessment of endurance performance (VO2max) are performed for the cross-sectional part of the study. All vascular diagnostics take place in the morning and under fasting conditions (visit 2 or 3). The endurance performance and the autonomic function is always performed in the afternoon (visit 2 or 3) to reduce within-day variability. Visit 1 and visit 2/3 are separated by at least 1 week to check inclusion/exclusion criteria. Visit 2 and 3 are separated by at least 1 day or no more than 2 weeks. After these three visits, the OSR group is randomized to take part in a 12-week HIIT or a control condition with general lifestyle recommendations. All participants have an equal likelihood of being assigned to treatment or control group. All assessments of the baseline examination are repeated in the follow-up after 12 weeks (Figure 1).

**Figure 1 F1:**
[figure not shown]
Study design, cross-sectional part (Part I) and randomized controlled trail (RCT) (Part II); HOA, healthy older active; HOS, healthy older sedentary; OSR, older sedentary at risk; CG, control group (standard recommendations for daily physical activity); HIIT, high intensity interval training.

### Inclusion criteria

Healthy men and women aged 50–80 years with:- active lifestyle: >9 MET/week (>3 h moderate walking/week) or- sedentary lifestyle: ≤ 3 MET/week (≤ 1 h moderate walking/week)- 18.5 ≤ BMI < 25.0 kg/m^2^Sedentary men and women aged 50–80 years with increased cardiovascular risk:- overweight or obesity (BMI ≥ 30 kg/m^2^) and- ≥one additional cardiovascular risk factor as described in Figure 2.

**Figure 2 F2:**
[figure not shown]
Inclusion criteria and risk factors for older sedentary at risk group (OSR).

### Exclusion criteria

Healthy men and women aged 50–80 years with:

History of cardiovascular, pulmonary or chronic inflammatory disease; blood pressure ≥140/90 mmHg during 24 h monitoring or any of the risk factors in Figure 2; current or past smoker; macular degeneration or glaucoma.

Sedentary men and women aged 50–80 years at risk:

Decompensated cardiovascular, pulmonary or chronic inflammatory disease; macular degeneration or glaucoma; compromising orthopedic problems.

### Setting

The RCT will be realized at the Department of Sport, Exercise and Health, Basel, Switzerland. This study is financially supported by the Swiss National Science Foundation (SNF) and approved by the Ethics Committee of Northwestern and Central Switzerland (EKNZ-2015-351). We registered this study on ClinicalTrials.gov (NCT02796976) in June 2016.

### Study procedures and ethical considerations

All participants are briefed verbally and receive information approved by the Ethics Committee of Northwestern and Central Switzerland (EKNZ) giving details on the study procedures, the RCT and the process of randomization. The study will be carried out in accordance to the protocol and with the principles stated in the Declaration of Helsinki and the Guidelines of Good Clinical Practice (GCP) (World Medical Association, 2013). This study protocol was design according the SPIRIT Guidelines.

All measurements and procedures applied in this study are non-invasive. Routine exercise ECG includes an exertional stress test as a medical necessity and safety precaution to evaluate cardiorespiratory health in all subjects. The OSR group undergoes a high intensity walking-based training program. HIIT has previously been applied in a wide range of patients including patients with coronary artery disease. The risk for cardiovascular events has been proven to be equally low for both HIIT and moderate continuous intervention strategies (Rognmo et al., 2012). Retinal vessel analysis includes mydriasis of one eye. Using a mydriaticum (Tropicamid 0.5%), the pupils are dilated and enable retinal vessel analysis. The eye drops can cause temporary discomfort, oftentimes a burning sensation for 1–2 min. Flickerlight exposure can potentially cause slight headaches. The collaborating ophthalmology department in Basel will offer back up at all times in the unlikely event of continuous discomfort.

All participants are committed to sign a consent form and will be informed about their right to withdraw from the study without any consequences. A study assistant will randomize the OSR group in an intervention or a control group by drawing a lot after the last pre-intervention assessment. Participants and investigators are blinded for the group membership during the pre-measurements. All participants are to be recruited from our outpatient department, the Metabolism Unit of the University Hospital Basel, Basel, Switzerland and, in addition, with postings on University webpages and advertisements in local newspapers. We aim to recruit the HOA group in running clubs and on running events in and around Basel. A total of 160 participants will be recruited for the study.

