## Imaging methods and course of measurements

### Macrovascular aging

#### Central pulse wave velocity

Carotid-femoral PWV (cfPWV), the gold standard for the measurement of arterial stiffness, is assessed by using a SphygmoCor® device (AtCor, Medical Pty Ltd, Sydney, Australia). The good intra- and interobserver reproducibility of this technique has been demonstrated in healthy populations and in patients with chronic kidney disease (Frimodt-Møller et al., 2006, 2008). After 10 min of rest, pulse waves are recorded using a high-fidelity tonometric transducer at two sites (right carotid artery and right femoral artery). Pulse wave travel distance is determined by subtracting the distance between the manubrium to the carotid artery from the distance between the femoral artery to the manubrium as previously described (Townsend et al., 2015). cfPWV measurements are considered to meet the quality control parameters if two consecutive measurements are visually acceptable and within 1 m/s of each other with a standard deviation of <10% (Sigrist et al., 2010). If this criterium could not be reached a third measurement was applied. The mean of all valid measurements represents the cfPWV value.

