### Microvascular aging

#### Static retinal vessel analysis (SVA)

The retinal microcirculation is easily accessible by using the Retinal Vessel Analyser (RVA, IMEDOS Systems, Jena, Germany) and a fundus camera (450 FF; Carl Zeiss, Jena, Germany). The technique allows for the analysis of the structure and function of retinal arterioles and venules. To measure retinal vessel diameters, we analyze three valid pictures from one eye with an angle of 50° and the optic disc in the center. The detailed procedure is described elsewhere (Hanssen et al., 2011). Briefly, retinal arterioles and venules, coursing through an area of 0.5–1 disc-diameter from the optic disc margin, will be identified semi-automatically at higher magnification using special analyzing software (Vesselmap 2, Visualis, Imedos Systems UG). Diameters will be averaged to central retinal arteriolar (CRAE) and venular (CRVE) equivalents, and the arteriolar-to-venular-ratio (AVR) will be calculated from the CRAE and CRVE. The inter-observer and intra-observer interclass correlation coefficient for the measurement of retinal vessel diameters ranges from 0.75 to 0.99 (Hubbard et al., 1999; Wong et al., 2004b).

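### The only blinding described ends before the lot is drawn, so nothing masks the 12-week measurements that decide the HIIT comparison

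*Protocol article*

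**What the plan says.** Under *Study procedures and ethical considerations*, the Protocol article gives the scope of blinding in one sentence: "Participants and investigators are blinded for the group membership during the pre-measurements". The sentence just before it fixes the time of allocation: "A study assistant will randomize the OSR group in an intervention or a control group by drawing a lot after the last pre-intervention assessment". *Study design* gives the same order: "After these three visits, the OSR group is randomized to take part in a 12-week HIIT or a control condition".

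The outcome data come later: "All assessments of the baseline examination are repeated in the follow-up after 12 weeks". *Statistical analysis* compares 12-week cfPWV between the two OSR arms by analysis of covariance, adjusted for the baseline value, and treats the secondary outcomes (retinal arteriolar and venular diameters) in the same way.

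On measurement, *Central pulse wave velocity* describes tonometry at the carotid and femoral arteries. Readings pass quality control "if two consecutive measurements are visually acceptable and within 1 m/s of each other", with a further limit of a standard deviation below 10%. If this is not met, a third measurement is taken, and the participant's value is the mean of the valid readings. For the retinal diameters, *Static retinal vessel analysis (SVA)* says that the vessels "will be identified semi-automatically at higher magnification using special analyzing software".

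The section on HIIT says that exercise scientists supervise every training session. The article does not say whether these people also carry out the follow-up measurements.

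**The concern.** Blinding is stated for a period in which no participant yet belongs to the HIIT or the control arm. The period in which knowledge of the arm can affect the result is the 12-week visit, and the statement does not reach it. Participants cannot be blinded to supervised training, so masking of assessors and readers is the available safeguard against measurement bias in this open comparison.

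This is more than a detail left to a fuller document. The article says who is blinded and when, and a team following it as written would have no instruction to mask anyone at follow-up. What is at stake is the credibility of a positive finding on cfPWV and on both retinal diameters, since some judgement enters each of them.

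**Working it through.** **1. Order of events.** Side by side, the sections give this sequence: three baseline visits (blinded), then the lot, then 12 weeks of HIIT or control, then repeat of all assessments (no blinding stated). The blinded period ends before the allocation exists.

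**2. Where judgement enters at 12 weeks.** For cfPWV, the operator decides whether a tracing is visually acceptable and so which readings count as valid. The numerical limits restrain this but leave room. Two readings 1 m/s apart have a standard deviation of 1/√2 = 0.71 m/s. Against the 11.5 m/s assumed for OSR in *Sample size calculation*, that is 0.71/11.5 = 6%, inside the 10% limit if that limit is read as relative to the mean. The third reading is triggered by rule and is not a free choice. For the retinal diameters, the measurement zone is fixed, but the pictures must be judged valid and vessel identification is only partly automatic.

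**3. Effect of one wrong rejection.** Take readings at m − 0.5 and m + 0.5 m/s, whose mean is m. If the upper one is wrongly rejected, the criterion is no longer met and a third reading follows. Assume the third is expected at m. The expected mean of the valid readings is then ((m − 0.5) + m)/2 = m − 0.25, a shift of 0.25 m/s for that participant.

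**4. The plan's own figure.** Inputs from *Sample size calculation*: difference 1.0 m/s, SD 1.5 m/s, baseline–outcome correlation 0.3, two-sided 0.05, 80% power.
- Residual SD = 1.5 × √(1 − 0.3²) = 1.431 m/s.
- Noncentral t with 2n − 3 degrees of freedom: power 0.798 at 33 and 0.810 at 34 per group.

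The stated 34 per group is reproduced.

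**5. False-positive rate under an assumed bias.** With no true effect and a net between-arm bias b, the noncentrality is b / (1.431 × √(2/n)). At n = 34 the standard error is 1.431 × √(2/34) = 0.347 m/s, and the smallest significant difference is about 0.69 m/s.

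| Assumed net bias (m/s) | Two-sided rejection, 34 per group | 40 per group |
|---|---|---|
| 0 | 5.0% | 5.0% |
| 0.1 | 5.9% | 6.1% |
| 0.2 | 8.8% | 9.5% |
| 0.3 | 13.6% | 15.3% |

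**6. How much selective rejection that would take.** At 0.25 m/s per affected participant, a net bias of 0.1 m/s needs 0.1/0.25 = 40% of one arm affected, all in the same direction and all with readings at the maximum permitted gap. By this route in one arm alone, the shift cannot exceed 0.25 m/s. A bias of 0.3 m/s would need opposite shifts in the two arms or another source, such as how the recording itself is made.

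**The case against.** The strongest reply has four parts.

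*The blinding sentence has a purpose.* A reader might infer that blinding before allocation protects nothing. That is wrong. Drawing the lot after the last baseline visit keeps the allocation unknown during eligibility decisions and during measurement of baseline cfPWV, which is the covariate. This stands.

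*The article does not say that follow-up assessors know the arm.* Nor does it say that the training supervisors measure cfPWV. A condensed article may leave staffing to the full protocol. This stands in part: actual exposure to bias is not shown. But the article does address blinding and confines it to baseline, so the scope as written needs correcting.

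*The measurement rules limit discretion.* The 1 m/s and 10% limits, the rule-triggered third reading and the fixed retinal zone all narrow what an operator can do. This stands, and it bounds the effect. A reader might infer that dropping one of two readings moves a value by 0.5 m/s, half the planned effect. The documents do not support this, because a rejected reading leads to a third, which halves the expected shift under the assumption in the working.

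*Travel distance is a separate matter.* Since cfPWV is distance over time, a reader might infer that girth loss in the HIIT arm could lower cfPWV through a shorter surface distance. The article gives no expected girth change and no effect of it on distance, and a masked assessor would record the same shorter distance. It is not part of this point.

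**Conclusion.** The point holds in a limited form. The stated blinding works as allocation concealment, and no section masks the 12-week cfPWV or retinal measurements on which the Part II contrasts rest. Because acceptance and reading keep an element of judgement, assessors who may know the arm can bias those contrasts.

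The documents give no estimate of such bias. If it amounted to a net 0.1 to 0.3 m/s, the two-sided false-positive rate would be about 6–14% at 34 per group in place of 5%. These bias sizes are assumptions, and selective rejection alone would have to be frequent and one-sided to reach even the lower end. The rates also rest on the plan's SD of 1.5 m/s and correlation of 0.3.

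It does not follow that the assessors are in fact unmasked or that a HIIT benefit would be false. The plan should be corrected because the gap lies in the primary contrast and is cheap to close. The sample size is unaffected.

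**What to change.** Amend the blinding statement in *Study procedures and ethical considerations* to cover follow-up:

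- The 12-week cfPWV is acquired, and accepted on site under the existing quality rule, by existing staff who do not supervise training and are not told the arm. Acceptance has to stay on site, because judging coded tracings later would make the third reading impossible.
- Stored retinal, intima-media thickness and echocardiography files are coded to hide arm and visit before they are read.
- Where masking is not feasible for a measurement, this is stated among the limitations in *Discussion and conclusion*, which at present do not mention it.

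The present sentence can stay if it is described as concealment of the allocation until baseline is complete. The cost is minor effort in rostering and file coding. It assumes that enough existing staff are not involved in training; if not, the limitation should be stated. Participants may still reveal their arm, so masking at the cfPWV visit will be imperfect.
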